### Assignment of interventions

#### Allocation

Following recruitment into the study, practices will undergo blinded, stratified random allocation into either an early or late intervention group using a minimization procedure. Early group practices will start receiving the intervention immediately after recruitment. Late group practices will start the intervention 6-months after the date of completing the initial baseline data collection to act as control for the group receiving the intervention first. To ensure that early and late study groups are similar, practices will be stratified based on region and practice size as determined by the number of full time equivalent (FTE) general practitioners (≤ 5 FTEs, > 5 FTEs). The randomization codes were generated using Minim randomization software [35]. Wherever possible, batches of two or more practices will randomised at the same time.

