### Statistical methods

Changes in practice performance relating to the primary outcome measure will be assessed between early and late intervention practice groups using multilevel mixed effects models to account for clustering as recommended for stepped-wedge cRCT designs [19, 20]. All quantitative outcome measures will be assessed for clustering, and if not significant may be further explored through uni-level multivariate methods (e.g. logistic regression to investigate factors affecting the proportion of consultations with interpreter use). However, if practice-level clustering is indicated, then the mixed models will include a cluster-specific random effect to deal with clustering at the practice level. In the main analysis the independent variables defined as fixed effects will be group allocation (1 = early, 0 = late), intervention status (0 = pre-intervention, 1 = post-intervention) and timepoint (0 = baseline for all practices, 1 = post intervention for early practices, pre-intervention for late start practices, 2 = 6 months post intervention for early practices, post intervention for late start practices, 3 = 6 months post intervention for late practices). Timepoint will be included as a categorical variable. In subsequent analyses, provider and practice level covariates thought to influence outcomes will be included to adjust for baseline differences between the two groups.

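### The main model omits region and practice size, on which allocation was minimised, and gives all three regions one time trend; the exposure is regional trends combined with unequal practice sizes

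*Protocol article*

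**What the plan says.** The Allocation section of the protocol article describes "blinded, stratified random allocation into either an early or late intervention group using a minimization procedure". It names the balancing factors: "practices will be stratified based on region and practice size as determined by the number of full time equivalent (FTE) general practitioners", with a cut at 5 FTE.

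The Statistical methods section then sets out the main model: "In the main analysis the independent variables defined as fixed effects will be group allocation (1 = early, 0 = late), intervention status" and timepoint, with four coded levels. On the last of these it adds: "Timepoint will be included as a categorical variable". Region and practice size are not in the list.

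Other variables come later: "In subsequent analyses, provider and practice level covariates thought to influence outcomes will be included to adjust for baseline differences between the two groups". None is named.

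If practice-level clustering is indicated, "the mixed models will include a cluster-specific random effect to deal with clustering at the practice level". For measures where clustering is tested, the section says that "if not significant may be further explored through uni-level multivariate methods".

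**The concern.** The article does not leave the main model open. It lists the fixed effects, and the list does not match the factors that drove allocation. The usual advice is to carry balancing factors into the analysis.

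The omission also means that one set of timepoint effects serves two Melbourne regions and one Sydney region. The Background says that settlement pathways vary across regions and jurisdictions, and Table 1 shows different partner organisations by region. Health assessment rates could therefore move differently over calendar time in the three regions, although the article does not say that they will. In a stepped-wedge analysis the time effect separates the intervention from the secular trend. If that effect is wrong for a region, the error can pass into the intervention estimate. At stake is the error rate of the primary test.

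**Working it through.** The plan states no figure on this point, so there is none to reproduce.

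**Inputs from the protocol article.** There are 36 practices (12 per region), 30 patients per practice and timepoint, an ICC of 0.05 and alpha 0.05 (taken as two-sided). Early practices are observed at timepoints 0, 1 and 2, and late practices at 0 to 3.

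**Assumptions, not in the documents.** Allocation is 18 early and 18 late, 6 of each per region. The outcome proportion is 0.5 and the model is linear on proportions. Regional shifts are independent at each timepoint, with SD 5 or 10 percentage points. The coefficient of variation (CV) of patients per practice is 0, 0.7 or 1.0. The share *f* of between-practice variance explained by region and size runs up to 1.0.

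**Step 1: what the model estimates.** Let D0, D1 and D2 be the early-minus-late differences at timepoints 0, 1 and 2. Intervention status differs between groups only at timepoint 1. Timepoint 3 has late practices only, so its own time effect absorbs it. With group and timepoint fixed and equal sizes, the status effect is D1 − (D0 + D2)/2.

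**Step 2: constant region and size effects.** These add the same amount to D0, D1 and D2, and so cancel. The standard error (SE) ratio, adjusted over unadjusted, is as follows.
- Equal sizes: 1.0000 for every *f* from 0.1 to 1.0.
- CV 0.7, ICC 0.05: on average 0.9998 (*f* = 0.3), 0.9994 (*f* = 0.6) and 0.996 (*f* = 1.0). The lowest single ratio was 0.990, at ICC 0.05 or 0.15.
- Single-level fallback: √(1 − ICC × *f*). At ICC 0.05 and *f* = 1 this is √0.95 = 0.975. At an assumed ICC of 0.15 it is √0.85 = 0.922.

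**Step 3: base SE.** The within-practice variance of a practice-period mean is 0.95 × 0.25/30 = 0.00792. The time contrast multiplies it by 1 + 1/4 + 1/4 = 1.5, and the two groups of 18 by 2/18. So the variance is 0.00792 × 1.5 × 2/18 = 0.00132 and the SE is 0.0363.

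**Step 4: regional shifts.** A shift in one region enters the contrast in proportion to the difference between that region's patient share in the early group and in the late group. With equal sizes and exact balance both shares are 1/3, and the shift cancels. With unequal sizes the variance of one share is approximately (1/18²)[6(2/3)² + 12(1/3)²]CV² = CV²/81. Taking two groups, three regions and the factor 1.5, the added variance is 3 × 2 × 1.5 × CV²/81 × SD² = CV² × SD²/9. If the model still reports 0.0363, the type I error is 2[1 − Φ(1.96 × 0.0363/true SE)].

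Example, CV 0.7 and SD 10 points: 0.49 × 0.01/9 = 0.000544. The true SE is √(0.00132 + 0.000544) = 0.0432, and 1.96 × 0.0363/0.0432 = 1.65, which gives 9.9%.

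The last two columns come from a simulation of the same layout with no true effect (2000 replicates, practice random intercept, variances treated as known).

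| Size CV | Shift SD | Added variance | Type I, formula | Type I, simulated as written | Simulated with region-by-timepoint |
|---|---|---|---|---|---|
| 0 | 5 pts | 0 | 5.0% | 5.3% | 5.3% |
| 0.7 | 5 pts | 0.000136 | 6.2% | 6.6% | 5.3% |
| 1.0 | 5 pts | 0.000278 | 7.5% | 7.3% | 5.1% |
| 0.7 | 10 pts | 0.000544 | 9.9% | 9.7% | 5.1% |
| 1.0 | 10 pts | 0.001111 | 14.9% | 12.4% | 4.2% |

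Formula and simulation agree except in the last row. There the formula is a rough approximation and the result depends on the shape of the size distribution. At 10 points, adding the terms lowers the empirical SE from 0.0437 to 0.0376 (CV 0.7) and from 0.0475 to 0.0368 (CV 1.0).

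**The case against.** The strongest reply is that the mismatch does little harm in the model as specified. Group and timepoint are fixed, so practice-constant factors drop out. Minimisation balances early and late practices within region, so a shift common to a region drops out too. A patient-level linear mixed model with equal sizes, exact balance and shifts of SD 5 points (150 replicates) supports this: estimates were identical with and without the terms, the SE ratio averaged 1.003, and rejection under the null was 4% both ways. This stands, but only for equal sizes and exact balance.

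The article does not secure those conditions. Thirty patients per practice is a sample size requirement, whereas the Data collection methods section has the extraction search all matching records. The primary outcome is further restricted to patients within 12 months of arrival. Balancing on a 5 FTE cut does not equalise the number of such patients.

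A second reply is that covariates are normally named in a statistical analysis plan. That holds for the unnamed later covariates, but not for the main model's fixed effects, which the article lists.

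Two stronger readings are tempting. A reader might infer that leaving out balancing factors makes the intervals clearly too wide, as in a parallel comparison at a single time. The planned estimate is a within-practice contrast, and Step 2 shows almost no loss. A reader might also infer that the later covariates will be picked after seeing the data. The article says only that they are thought to matter; it does not say when they are chosen, and it does not exclude region or size.

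**Conclusion.** The point holds as a mismatch between allocation and main model, with one material consequence. Region and size as main effects would add almost nothing to precision, and they would not help against regional trends, since a constant effect cannot absorb a shift that changes over time. The exposure is the single shared time trend. With regional shifts of SD 5 to 10 points and size CV of 0.7 to 1.0, the nominal 5% test runs at about 6 to 12.5%, and region-by-timepoint terms bring it back to about 5%.

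This is conditional. The documents give neither the size of any regional trend nor the spread of practice sizes, and with equal sizes and exact balance the problem disappears. The figures rest on a linear model at a proportion of 0.5 with known variances; a logistic mixed model was not examined.

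**What to change.** State in the Statistical methods section that the main model for the primary outcome includes region (3 levels) and practice size (≤5, >5 FTE) as fixed effects, with region-by-timepoint terms. Keep all other provider and practice covariates for analyses labelled secondary. Apply the same rule to any outcome analysed with the single-level fallback.

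No new data are needed, since allocation already uses both variables. The model gains up to 9 parameters: 2 for region, 1 for size and 2 × 3 = 6 for region-by-timepoint. That is not negligible with 36 practices, and the terms at timepoint 3 rest on late practices only. If regional trends are absent, the standard error is about 1 to 3% wider with unequal sizes and unchanged with equal sizes. If the investigators prefer the shorter model, they should give the reason and report the model with region-by-timepoint terms as a pre-specified sensitivity analysis.

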### Qualitative analysis

A Research Fellow with qualitative methods expertise will read de-identified interview transcripts, facilitator diaries, and other documents. We will begin by developing a preliminary coding template, based on the initial reading and familiarisation with the raw data, as well as a priori broad theoretical concepts from Stange and Glasgow’s Context Tool [39] and May’s Normalisation Process Theory [26, 40]. We will refine and expand on the preliminary coding template following the standard qualitative techniques of immersion, crystallisation and constant comparison which involves repeated cycles of detailed examination of data, followed by reflection, identification, and articulation of themes and concepts and purposive refinement of existing theories. Interpretive insights are recorded to generate a ‘thick’ description of the findings and their context and include extracts from raw data and discussed with the team. Individual member of the research team will independently code a number of sources to test for reliability and the appropriateness of the final coding template.

We will use matrices to help organize and analyse the data and generate case descriptions [41]. We will evaluate the impact of the practice facilitation approach by exploring mechanisms for changes in practice routines across the four foci of the intervention, and then further considered against:Practice outer context: refugee background population in the area, links with external environment.Practice inner context: practice size, practice staff, time required to recruit the practice, proportion of refugee patients, staff/patient language concordance.Intervention: practice’s level of engagement with the intervention.Facilitator and research officers: the time research officers spend engaging the practices and troubleshoot issues arising with implementation.

Reliability will be informed by parallel collection of the same categories of data by multiple researchers, inter-rater comparisons of data coding decisions and clearly defined measurement procedures. Accuracy of the findings is achieved through the use of multiple data sources, and the triangulation of qualitative data with surveys and de-identified aggregate clinical data [42].

### Data monitoring

Minimal risks were evaluated with this study and hence a data monitoring committee was not needed.

#### Harms

Harms within the study are not anticipated, however in the event that they do arise, practices will inform the research officer and the practice may have to be withdrawn from the study. Ethics procedures are in place such that if a participating provider becomes distressed at interview they will be referred for psychological support.

#### Auditing

No plans for auditing have been made for this study.

### Ethical considerations

#### Research ethics approval

The project was approved by the Monash University Human Research Ethics Committee (Ref:10086), Monash Health Human Research Ethics Committee (Ref: 17-487L), South West Sydney Local Hospital District Human Research Ethics Committee (Ref: LNR/17/Lpool/391) and La Trobe University Human Research Ethics Committee (Ref: S17–138). Original protocol approvals were granted in September 2017 before project commencement. All protocol amendments require agreement by all authors, and will be submitted to and approved by the respective Human Research Ethics Committee using the appropriate ethics amendment forms. As a practice-based intervention designed to achieve organisational change, there was no direct contact with refugee clients, hence ethical concerns that may arise about conducting research about this vulnerable group were not applicable.

#### Consent or assent

Written informed consent will be obtained from participants.

#### Confidentiality

Data will be stored on password protected secure drives on Monash University servers, and/or in secure filing cabinets for the duration of the study. Data will be cleaned and de-identified by each site prior to secure transfer to the biostatistician.

#### Access to data

Investigators are data custodians during and after the project. Custodians need to be informed about any data management/analyses.

#### Ancillary and post-trial care

As there are low risks of harm with this study, ancillary and post-trial care has not been organised.

### Dissemination policy

The results of this study will be disseminated via publication in a peer reviewed journal and presented at a relevant conference. The investigators have adopted an authorship protocol based on the International Committee of Medical Journal Editors recommendations [43]. Final decisions in case of disputes regarding authorship rest with the study’s principal investigator. Partner agencies will be acknowledged in all publications. Professional writers will not be used. Findings will be shared with each Regional Partnership Team, and summaries of key findings will be shared with participating practices and other interested stakeholders. Public access will be provided for individual participant data that underlie the results reported in study publications, after de-identification (text, tables, figures, and appendices). We will also make available the statistical analysis plan and relevant statistical code. Availability will begin 6 months after and end 36 months following article publication and will be for proposals that have been approved by an independent review committee. Qualitative data will not be made publicly available.

## Discussion

A co-designed, practice facilitation intervention is an innovative approach to improve key refugee background patient outcomes in 36 practices in regions with the highest refugee settlement in Australia.

The findings of the research described in this paper will generate evidence for the effectiveness and limitations of a practice facilitation approach to quality improvement in general practice. This will add to the evolving body of knowledge around the implementation of practice facilitation, particularly whole-of-practice changes that impact on access to quality primary health care for vulnerable populations. It will also generate evidence about the approach to facilitate improvements in the delivery of primary care to people of refugee background.

Data on the intervention will generate valuable knowledge concerning the effectiveness of outreach practice facilitation in optimising the primary care of people of refugee background in Australia. If successful, it will deliver quality, accessible and coordinated PHC care to refugees. Primary care clinicians, especially those working within general practice clinics will benefit from insights for improving refugee identification, health assessment, interpreter use and referral. Potential solutions can be adapted to local contexts to address a local health system’s priority gaps and will ultimately assist the Australian health system to integrate care and reduce the burden on refugee focused health services to meet the needs of this vulnerable population. Additional benefits are likely to flow from inter-sectoral partnerships between academics, Refugee Focused Health Services, mainstream general practice clinics, settlement services, state governments and primary health care organisations.

## Data Availability

Not applicable.

## Abbreviations

cRCT: cluster Randomised Controlled Trial
FTE: Full Time Equivalent
GP: General Practice
MBS: Medicare Benefits Schedule
NWM: North West Melbourne
PDSA: Plan/Do/Study/Act
PHC: Primary Health Care
PHN: Primary Health Network
RPT: Regional Partnership Team
SEM: South East Melbourne
SWS: South West Sydney
